## Safety measures and end point

The physical activity researcher (RM) has extensive experience in conducting physical activity program evaluations in adults and children and the accredited practising dietitian (DT) has experience in conducting a telehealth nutrition intervention in older adults with AMD which included the provision of appropriate nutrition advice and counselling. The co-authors (NB and CJ) also have firsthand experience administering WTL and WTL-Z and will provide oversight on the study as well. The research team member facilitating the MINGLE program will have an exercise-related qualification and accreditation to practice. Rated a low-risk study, adverse events are unlikely to occur. However, safety endpoints will be indicated where participants report or present with persistent pain or injury after performing the exercises. In this case, appropriate documentation will be completed, and the participant will be excused from participating in the exercise sessions until they completely recover and advised to seek medical and/or allied health advice where appropriate.

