## Introduction

Age-related macular degeneration (AMD) is the leading cause of vision loss and blindness in high income countries with an expected global prevalence of approximately 300 million by 2040 [1]. Vision loss also has wider health impacts and has been associated with higher rates of loneliness, reduced quality-of-life, and increased falls risk [2–4]. Among older adults in particular, the research literature shows that loneliness is more prevalent in visually impaired elderly than normal sighted elderly [3, 4]. Examples of this include a Dutch study which reported a significant difference of 21% more visually impaired older adults experiencing feelings of loneliness compared to normal sighted older adults (50% vs. 29%, respectively) [3]. Another study in Norway showed that among adults aged ≥ 66 years, there were 8.7% and 8.6% more visually impaired elderly suffering from moderate and severe loneliness, respectively, compared to the general Norwegian population of elderly [4].

Feelings of loneliness have also been associated with depressive symptoms [5], where the latter is already prevalent in up to 63% of visually impaired older adults including individuals experiencing minimal vision loss [2]. Moreover, persistent loneliness can also lead to poorer lifestyle behaviours [6, 7], which is particularly concerning for people with AMD, as growing research evidence supports an association between lifestyle risk factors such as a poor diet and low levels of physical activity with an increased risk of AMD development and/or progression [8–10]. Persistent loneliness has also been linked to other health outcomes including dementia and cardiovascular health risks [6, 7, 11, 12]. Therefore, there is a strong need for evidence-based intervention programs focused on reducing loneliness in visually impaired older adults, such as those diagnosed with AMD.

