Amongst people with AMD, positive participant responses to virtual programs have also been reported in another evidence-based intervention developed by our group, which aimed to improve the dietary intakes of people with AMD through telehealth nutrition intervention [17]. This telehealth intervention involved the provision of an evidence-based workbook on nutrition and AMD links, together with monthly individual phone calls with a dietitian over four months, which significantly improved the participants’ dietary intake of nutrient-rich dark green leafy vegetables and legumes and reduced consumption of packaged and processed foods [17].

To address the impacts of vision loss caused by AMD, including the increased prevalence of loneliness, depression and falls risk, as well as to improve AMD-related lifestyle risk factors (poor diet and physical inactivity), we aimed to build on our prior research by developing a holistic program called MINGLE (Movement, Interaction and Nutrition for Greater Lifestyles in the Elderly) and piloting this novel program in a sample of older Australian adults with AMD. Therefore, this study aims to: 1) develop the MINGLE program tailored to AMD patients, by incorporating the successful aspects of existing evidence-based interventions developed by our group (WTL-Z and a dietary intervention [17]); and 2) deliver the MINGLE program online via Zoom [18] in a non-randomised group of AMD patients. Although our prior research has shown that online delivery of WTL-Z can effectively reduce loneliness and depression, this study was conducted in normal sighted older adults residing in the UK. Hence, this pilot study is needed to evaluate the acceptability and feasibility of delivering the online MINGLE program in visually impaired older adults. The aims of this study will be achieved through two phases. Phase 1 will conduct semi-structured interviews with AMD patients to identify the barriers and facilitators to participating in the proposed MINGLE program; to determine the participants’ thoughts about MINGLE and what they would change or would like included in the program and to accordingly modify the proposed MINGLE program to better suit the needs of people with AMD. Phase 2 will then involve a non-randomised pilot trial of the modified MINGLE program in AMD patients to determine the program’s acceptability and feasibility and its preliminary efficacy.

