	What do you think might be the best way to keep participants motivated and committed to the 10-week MINGLE program?	How could we have made the program more motivating and easier to commit to.
	Do you have any further comments regarding the MINGLE program or anything else we have spoken about today?	Do you have any other suggestions or feedback regarding the MINGLE program?

### Intervention in Phase 2

Using Phase 1 findings, the proposed MINGLE program will be modified to better suit people with AMD. The proposed MINGLE program, adapted from WTL and the dietary telehealth intervention [17], will run for 1-hour per week for 10 weeks online via Zoom. Participants will be divided into subgroups based on participant preference to available session timings (e.g., morning/afternoon). An overview of the proposed MINGLE program has been summarised in Table 2. Briefly, each session will include 10 minutes of informal socialising; 30 minutes of physical activity; and 15 minutes of nutrition education. The physical activity session will not require any equipment other than a chair and will be facilitated by a research team member with an exercise-related qualification. Each physical activity session will include: 2-minute mindful breathing, 12-minute warm-up (e.g., stretching and bodyweight strengthening exercises), 7-minute moderate-to-vigorous intensity shadow boxing, and 9-minute cool down (e.g., bodyweight strengthening, balance exercises). The intensity of the exercises will be self-evaluated using the Borg Rating of Perceived Exertion (RPE) Scale [21]. Modified versions of the exercises will also be demonstrated by the researcher for participants who find the exercises too easy or difficult. The AMD-related nutrition education will focus on evidence-based content on appropriate use of nutritional supplements (e.g., Age-Related Eye Disease Study (AREDS) and key food groups to incorporate as part of the habitual diet according to the Australian Dietary Guidelines [22]. The format of this nutrition educational content will alternate between presentations by the researcher and facilitated group discussions.

**Table 2 pone.0267581.t002:** Overview of the proposed MINGLE program.

Contents		Duration (min)
Informal socialisation	Session 1: introduction of participants and facilitators; discussion of program expectations	10

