
In addition to the AFRIS, the following approaches will be used to assess the acceptability and feasibility of the MINGLE program. 1) A 30-minute feedback discussion to reflect on the MINGLE program will be held immediately after the tenth session of the program. Participants will be invited to join the discussion by remaining online after completing their tenth session. Participants will be asked to reflect on a range of topics including their program experience; suggestions on how to improve the program; and the program’s potential for a large-scale roll-out. 2) A short feedback form will be included in the post-intervention questionnaire. This will include open- and close-ended questions covering level of satisfaction with the program, self-determined adherence to the program, and general feedback (e.g., suggestions to improve the program). 3) Attendance data will also be collected on all participants to allow for reporting on: the number sessions attended, completed sessions (‘dose’ of intervention received), and reasons for missed sessions. The session content will be tracked via checklists completed after each session allowing for reporting on the extent to which the intervention content is delivered per protocol and percentage of participants engaging/completing the activities.

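### The stated safety endpoint covers persistent pain or injury, so non-injurious falls, near-falls and transient symptoms lie outside it, and no other stated measure records fall events

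*Protocol article*

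**What the plan says.** The section Safety measures and end point of the protocol article sets the expectation that "Rated a low-risk study, adverse events are unlikely to occur", and then gives one trigger: "safety endpoints will be indicated where participants report or present with persistent pain or injury after performing the exercises". When that happens, "appropriate documentation will be completed, and the participant will be excused from participating in the exercise sessions until they completely recover", with advice to seek care where appropriate. No other event is named as a safety endpoint.

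The Introduction says that vision loss "has been associated with higher rates of loneliness, reduced quality-of-life, and increased falls risk". It then lists the impacts of AMD that the programme is meant to address, "including the increased prevalence of loneliness, depression and falls risk".

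Intervention in Phase 2 describes weekly one-hour Zoom sessions for 10 weeks, led by a team member with an exercise-related qualification. Balance exercises appear both in that text and in Table 2. The text also lists "7-minute moderate-to-vigorous intensity shadow boxing", which Table 2 does not.

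On recording, the Measures section says: "The session content will be tracked via checklists completed after each session". The stated purpose is to report how far content was delivered as planned and what share of participants engaged in or completed the activities.

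**The concern.** The safety definition does not match the rationale. The protocol singles out falls risk as a feature of this population and as a target of the programme, then defines its safety endpoint by pain or injury. Someone who loses balance and recovers, falls without being hurt, or stops because of a passing symptom gives no reportable event under that sentence.

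These are the events a small exercise pilot in visually impaired older adults is best placed to observe, since injurious events may be too rare to appear in 52 people. The post-programme discussion asks participants about the programme's potential for large-scale roll-out. A summary showing no safety endpoints could be read in that context as reassurance about falls, although falls without injury were never within what was counted.

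**Working it through.** **Step 1. Does any other stated measure record fall events?**

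| Source in the protocol article | What it captures | Fall events? |
|---|---|---|
| Safety measures and end point | Persistent pain or injury after the exercises | Only through a resulting injury |
| FES-I (Measures) | Concern about the possibility of falling | No |
| AFRIS (Measures) | Attitude to the intervention | No |
| Session checklists (Measures) | Content delivered; engagement and completion | Not stated |
| Attendance data (Measures) | Sessions attended and completed; reasons for missed sessions | Only if an event led to absence |
| Outcome measurement | Recruitment, adherence, attrition, AFRIS, feedback, participant-reported scales | No safety count listed |
| Data collection and analysis plan, Phase 2 | Descriptive statistics for acceptability, feasibility and pre-post changes | No safety count listed |

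The Abstract lists falls risk among the variables collected, but the instrument behind it is the FES-I, a scale of concern. No row records a non-injurious fall or a near-fall as an event.

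**Step 2. What the endpoint wording covers.** An injurious fall would plausibly be reported as an injury. Two things are unclear: whether *persistent* qualifies injury as well as pain, and whether *after* the exercises includes events during a session. On either reading, non-injurious falls, near-falls and transient symptoms are outside.

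**Step 3. The plan's own figure.** The Phase 2 sample size is 52, for a pre-post change in loneliness with d = 0.4 and 80% power. The article states neither alpha nor sidedness. Assuming a two-sided 0.05 paired t-test (noncentral t), the smallest n is 52, with power 0.808. The figure reproduces; the safety point does not depend on it beyond supplying n.

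**Step 4. What 52 participants could show if the events were recorded (illustration).** With zero events in n independent units, the one-sided 95% upper bound is 1 − 0.05^(1/n).

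- Per participant, n = 52: 1 − 0.05^(1/52) = 5.6%. The upper limit of a two-sided 95% interval is 1 − 0.025^(1/52) = 6.8%.
- Per session at full attendance, n = 52 × 10 = 520: 1 − 0.05^(1/520) = 0.57%.
- Per session at 80% attendance (the commitment level in the Phase 2 exclusion criteria), n = 0.8 × 520 = 416: 1 − 0.05^(1/416) = 0.72%.

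The per-session figures treat sessions within a person as independent, which is optimistic.

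The chance of seeing at least one event among 52 is 1 − (1 − p)^52. The documents give no event rate, so p is assumed:

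| Assumed risk per participant | Chance of at least one event in 52 |
|---|---|
| 1% | 41% |
| 2% | 65% |
| 5% | 93% |
| 10% | 99.6% |

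**Step 5. What follows.** Each bound applies only to event types that are recorded. A zero count under the present definition could bound injury or persistent pain. It could not bound non-injurious falls, near-falls or interrupting symptoms.

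**The case against.** The strongest reply is that the sentence does not say *only*. The article condenses a fuller protocol, and adverse-event definitions and forms are commonly left to that document. This stands against any claim that falls will go unrecorded: a reader might infer that, but the article does not establish it. It does not remove the point, because the article states a definition itself, and that definition is narrow for its own rationale.

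A reader might also infer that all falls are missed. They are not, since a fall causing injury would plausibly qualify.

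Nor do the documents support calling the exercise unsupervised. Sessions are live and led by a facilitator with an exercise-related qualification and accreditation, modified exercises are demonstrated, and a Research Assistant evaluates adherence at each session. Participants need PARQ+ or physician clearance, and the exclusion criteria screen for ability to walk for exercise and for contraindications. The article does not say that participants exercise at home; that is inferred from Zoom delivery.

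Indirect channels exist: reasons for missed sessions, the weekly recap that includes reflection on the exercises (Table 2), and a focus-group question about concerns while participating (Table 1). They may surface some events but do not give a count.

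The programme is described as proposed and open to change after Phase 1, and shadow boxing is absent from Table 2, so the argument should rest on the balance exercises, which are in both descriptions. Finally, no section plans a formal safety conclusion or a safety criterion for roll-out. The harm described is therefore a risk of misreading, not a planned inference.

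**Conclusion.** The point holds in a limited form. The stated safety endpoint, and the documentation tied to it, are confined to persistent pain or injury. Non-injurious falls, near-falls and transient symptoms that interrupt exercise are outside it, and no other stated measure records fall events, although the rationale names falls risk. A report of zero safety endpoints would say nothing about those events.

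The size of the gap cannot be estimated, because the documents give no event rate. The zero-event bounds (5.6% per participant; 0.57% to 0.72% per session) show what recording could offer, not how much is lost. They assume complete recording for all 52 participants, and the per-session bounds also assume independent sessions. The conclusion rests on the article as it stands; if the full protocol already records these events, only the wording of the safety section needs alignment. This is a cheap improvement, not a flaw that undermines the pilot.

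**What to change.** Add separate recording items to the existing post-session checklist: any fall, near-fall, pain, injury or symptom that interrupted exercise, during the session or since the last one. Report the counts descriptively, per participant and per attended session.

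Keep these items apart from the rule in Safety measures and end point. There, meeting the endpoint leads to being excused from exercise, so simply widening the endpoint would also widen that rule. How events are handled clinically is for the sponsor to decide.

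Reconcile the wording of the safety definition with the falls-risk rationale in the Introduction, and state whether *persistent* applies to injury and whether events during a session count.

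The cost is about a minute more per session and one descriptive table, with no added visits or staff.

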## Patient and public involvement

This study will have patient involvement in the adaptation of the MINGLE program. Patient involvement will occur in Phase 1 of the study where semi-structured interviews are conducted to identify the facilitators and barriers to participating in an online lifestyle intervention program to help inform the development of MINGLE. Patients will not be involved in the recruitment or conduct of the program itself. Overall results will be disseminated to consenting participants at the end of the study as a one-page lay summary.
